## Abstract

**Background:**

There is increasing evidence for early, active rehabilitation to enhance motor function following early brain injury. This is clear for interventions targeting the upper extremity, whereas passive treatment approaches for the lower extremity persist. The purpose of this trial is to evaluate the effectiveness of early, intensive rehabilitation targeting the lower extremity and delivered in a parent-therapist partnership model for children with perinatal stroke.

**Methods:**

We describe a protocol for a waitlist-control, single-blind, mixed methods effectiveness randomized controlled trial, with an embedded qualitative study using interpretative description. Participants are children with perinatal stroke aged eight months to three years with signs of hemiparesis. Participants will be randomly allocated to an immediate ELEVATE (Engaging the Lower Extremity Via Active Therapy Early) intervention group, or a waitlist-control group, who will receive usual care for six months. The ELEVATE intervention involves one hour of training four days per week for 12 weeks, with a pediatric therapist and a parent or guardian each delivering two sessions per week. The intervention targets the affected lower extremity by progressively challenging the child while standing and walking. The primary outcome measure is the Gross Motor Function Measure-66. Secondary outcomes include the Pediatric Quality of Life Inventory™, Young Children's Participation and Environment Measure, and an instrumented measure of spasticity. A cost-effectiveness analysis and qualitative component will explore benefit to costs ratios and parents’ perspectives of early, intensive rehabilitation, and their role as a partner in the rehabilitation, respectively.

**Discussion:**

This study has the potential to change current rehabilitation for young children with perinatal stroke if the ELEVATE intervention is effective. The parent interviews will provide further insight into benefits and challenges of a partnership model of rehabilitation. The mixed methods design will enable optimization for transfer of this collaborative approach into physical therapy practice.

**Trial registration:**

ClinicalTrials.gov NCT03672864. Registered 17 September 2018.

**Supplementary Information:**

The online version contains supplementary material available at 10.1186/s12887-022-03525-6.

## Background

Perinatal stroke occurs between 20 weeks gestation and 28 days postnatal life and is the leading cause of unilateral cerebral palsy [1] with an estimated incidence of 1 in 1600–3000 live births. Perinatal stroke may result in life-long motor impairments [1–4]. For example, the children typically have limitations with walking, which results in abnormal loading of the joints, premature musculoskeletal problems, reduced physical activity, and participation [5, 6]. Further, the sequelae from perinatal stroke can have a profound impact on family well-being [7].

Recent evidence indicates active interventions improve function [8], while passive interventions, such as bracing and botulinum toxin A injections, provide only short-term gains with unknown or suboptimal longer-term outcomes [9–11]. Early, intensive rehabilitation for the upper extremity has gained acceptance, but active rehabilitation for the lower extremity remains infrequent with little standardization between therapists and centres [12].

Our preliminary efficacy trial indicated that the ELEVATE (Engaging the Lower Extremity Via Active Therapy Early) intervention resulted in significantly greater improvements in gross motor function compared to a control group receiving usual care [13]. Children less than three years old with perinatal stroke tolerated one hour of intensive lower extremity activity, four days/week for twelve weeks.

Sufficient intensity of neurological rehabilitation is important [14], but it is often neither feasible nor cost-effective for physical therapists to administer high-intensity training for a prolonged period. Achieving this intensity is often better achieved by children’s parents or guardians, especially with very young children [15, 16]. Involvement of the family is essential for enhancing child outcomes [17], but there are limited reports of parents’ experiences with conducting home rehabilitation programs, especially as partners in therapy [18]. Furthermore, while family centered care advocates for parent-clinician partnerships, clinicians are cautioned against ‘downloading’ professionally driven interventions to families [19]. This study is a concurrent mixed methods design; the qualitative study will explore the parents’ perspectives of the intervention and their experiences as a partner in rehabilitation.

The purpose of this trial is to evaluate the effectiveness of early, intensive rehabilitation delivered using a parent-therapist partnership model for children with perinatal stroke. The trial was designed in collaboration with parents and therapists to build on our findings in the laboratory and determine if the intervention is effective in a real-world setting. We hypothesize that, as compared to a control group receiving usual care, young children with perinatal stroke and unilateral cerebral palsy (CP) who receive intensive lower extremity training delivered in a parent-therapist partnership will demonstrate greater improvement in gross motor function.

## Methods

### Experimental design

This is a three-centre (Edmonton [primary site], Calgary, and Ottawa), mixed methods study in which a qualitative study is embedded in a waitlist-control, single-blind randomized controlled trial (RCT). The children will be randomly allocated to either the Immediate Intervention Group (treatment) or the Waitlist-control Group (usual care) with follow-up (Fig. 1). The Immediate Intervention Group will undergo the three-month ELEVATE intervention immediately following randomization. The Waitlist-control Group will delay treatment for six months before initiating the ELEVATE intervention. The primary time point of interest is at six months in the study (Fig. 2). All children will undergo monthly assessments for 12 months in the study and will also be assessed at age four years of age to evaluate longer-term effects of training.

**Fig. 1 Fig1:**
[figure not shown]
SPIRIT Flow Diagram. Participants are randomly allocated to either receive the ELEVATE intervention immediately (Immediate Group) or delay the intervention for 6 months (Waitlist-control Group) to serve as a usual care control

**Fig. 2 Fig2:**
[figure not shown]
Experimental Design with Measurement Time Points. Participants are randomly allocated to either receive the ELEVATE intervention immediately (Immediate Group) or delay the intervention for 6 months (Waitlist-control Group) before they are offered the optional ELEVATE training. Children undergo monthly assessments for 12 months (including 9 months of follow-up for the Immediate Group and 3 months of follow-up for the Waitlist-control Group). Outcome measures are obtained as indicated by arrows and stars. GMFM-66: Gross Motor Function Measure-66; PSAD: Portable Spasticity Assessment Device; PedsQL CP: The Pediatric Quality of Life Inventory™ module for cerebral palsy; YC-PEM: Young Children's Participation and Environment Measure; RUQ: Resource Use Questionnaire

### Inclusion criteria

children ages 8 months to 3 yearsmedical history and physical exam consistent with perinatal strokehemiparesis in the upper and/or lower extremityagreement from parent/guardian to adhere to the training and testing schedule

### Exclusion criteria

bilateral motor impairmentepileptic seizures that could interfere with trainingcognitive, behavioural or developmental impairments that preclude participation in the protocolbotulinum toxin A injections or surgery in the lower extremities within the previous six monthsconcurrent casting during the intervention phase (including constraint-induced movement therapy with casting)diagnosis associated with neurological/developmental regressionparent unable to communicate (verbal and written) in English or French

### Randomization and stratification

Participants will undergo baseline assessments before randomization (Fig. 1). The randomization sequence was generated in Edmonton by a statistician. We used a permuted block design with a block size of 2–4. Randomization was stratified by city to ensure that the numbers allocated to the intervention and control groups will be roughly equal at each site. Their assignment is concealed until baseline assessments are complete, and are made available to the study sites through Research Electronic Data Capture (REDCap).

### Intervention

ELEVATE [13] will be administered one hour/day, four days/week, for twelve weeks. The ELEVATE intervention follows principles of motor learning and neuroplasticity [14], with high repetition of child-initiated activity. The activities will focus on weight-bearing on the feet with the aim to maximize recruitment of multiple, lower extremity muscle groups, especially on the affected side. Training may include activities such as kicking, squatting, navigating obstacles and walking on ramps and stairs. Children will train in soft-soled slippers, without braces or orthotics, to enhance active use of muscles throughout the lower extremity. Children who are not yet walking will be encouraged to walk with support while incorporating activities that increase weight bearing through the affected lower extremity and challenge their balance. As children begin to walk independently, their mobility will be further challenged by walking at different speeds, changing walking direction, and walking on unstable or more physically-demanding surfaces. The aim for intervention sessions is an hour of activity, which is anticipated to result in approximately 1000–3000 steps (as measured by step counters; Actigraph, FL), depending on the child’s age and ability [13]. Small ankle and foot weights (110 g and 20 g increments, respectively) will be used to increase work of the affected lower extremity, once children tolerate one hour of training [20]. Children with hemiparesis resulting from perinatal stroke typically walk asymmetrically, and adding ankle and foot weights to the affected lower extremity increases asymmetry of walking, which is necessary to induce learning [21]. Once children demonstrate more symmetrical gait with the weights, the amount of weight is increased to induce further learning [22].

### Parent therapist partnership

This effectiveness trial is designed to deliver the ELEVATE intervention by parents and therapists working in partnership. The partnership was considered an ideal model because it provides a high dose of intervention while supporting parents as partners in the rehabilitation process [23]. Physical therapists or physical therapy assistants working in public or private outpatient pediatric therapy centres will provide the intervention. The parent and therapist will each deliver two days of intervention per week. The parent will attend the intervention sessions with the therapist, thereby providing opportunities for observation and discussion. This will include reinforcement of the training principles, feedback on training and opportunities for progressions. Parents will be provided with a training manual describing suggested training activities [20].

### Intervention fidelity across centres

All treating therapists will be trained by the Principal Investigator and research physical therapist before the trial. Training will include background on activity-dependent neuroplasticity and an overview of the efficacy of early intensive rehabilitation. Practical training will include video examples and hands-on practice with young children. Treatment fidelity will be assessed throughout the trial using step-counts during intervention sessions, monthly video documentation, and biweekly meetings with staff at each site. Additional training sessions will be provided if training therapists indicate low confidence with the intervention.

## Outcomes

### Primary outcome measure

#### Gross motor function

The Gross Motor Function Measure-66 (GMFM-66) is the primary outcome measure, a criterion-referenced observational measure for assessing gross motor function in children with CP [24]. It has been validated for children > 0.5 years old and is a gold standard for measuring gross motor function in children with CP [25]. The assessing therapists will be pediatric physical therapists from the community trained by study personnel to administer the GMFM-66 and are masked to the child’s group assignment. All parents will be informed not to disclose the child’s group assignment to the assessing therapist. All assessments will be videotaped for reference. The GMFM-66 will be administered twice at baseline and monthly thereafter, for a total of 14 measurements per child. The two measures at baseline will be averaged to provide a more reliable estimate.

### Secondary outcome measures

#### Quality of life

Quality of life of the participants and their parents will be quantified at entry to the study, and again every 3 months using the Pediatric Quality of Life Inventory™, module for cerebral palsy (PedsQL CP) [26]. The PedsQL CP will be administered via online self-report through REDCap, or over the phone if respondents require assistance. The PedsQL is reliable and sensitive [26] and has been used extensively for this population. The children in this study are too young to self-report, so a parent proxy will be used. The scales in the CP module used are those recommended for children up to four years old [26]. The PedsQL also has a 36-item scale to measure the impact of a child’s health condition on the family, called Family Impact Module (PedsQL FIM). The scale has been widely used for parents of children with chronic health conditions, including perinatal stroke [7]. Three scores will result from this module, which reflect the parents’ health-related quality of life, family functioning and a total score.

#### Resource use and costing

Costs related to lower extremity therapy as well as resources used for treatment and management of the child’s cerebral palsy will be included over the study period, similar to a previously reported protocol [27]. The child will be the unit of analysis and utilization incurred by the participant, caregivers and/or the healthcare system will be assigned to the child for analysis. The Resource Use Questionnaire (RUQ) is a tool validated for use in participants with neurodevelopmental disabilities [28, 29] and will be used to collect information regarding resource use and out-of-pocket costs (e.g. physical or occupational therapy, materials and equipment, child-focussed recreation activities, etc.).

The RUQ will be administered at baseline, six months, the end of the one year study period and at the four-year-old follow up. The total cost per participant per month will be calculated and used in extrapolation. For the healthcare system perspective, costs will include physical or occupational therapy, child-focused recreation activities and additional services related to the child’s care paid for by the public healthcare system. For the societal perspective, costs will include all costs for the healthcare system perspective as well as parent lost productivity and parent out-of-pocket costs. For analysis using the societal perspective, a human capital approach [30] will be used to monetize lost caregiver productivity. Parent reports on the RUQ will include out-of-pocket costs for additional services, child-focused recreation activities, and materials and equipment. Lost productivity and out-of-pocket costs will be summed for the family of each participant to obtain total lost productivity and out of pocket costs for each participant over the study period.

The cost of the ELEVATE intervention will be estimated from the compensation to therapists including training, administration of the ELEVATE intervention and the cost of any materials and supplies associated with the intervention.

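### The societal cost-effectiveness ratio prices parent time only as lost productivity or out-of-pocket cost, so parent hours on ELEVATE that displace no paid work appear to carry no cost

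*Protocol article*

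**What the plan says.** Resource use and costing sets out the cost items in three steps.

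- **Intervention cost:** "The cost of the ELEVATE intervention will be estimated from the compensation to therapists including training, administration of the ELEVATE intervention and the cost of" materials and supplies. Parent time is not named.
- **Societal perspective:** "costs will include all costs for the healthcare system perspective as well as parent lost productivity and parent out-of-pocket costs".
- **Valuation of parent time:** "a human capital approach [30] will be used to monetize lost caregiver productivity".

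The same section has a general attribution rule: "utilization incurred by the participant, caregivers and/or the healthcare system will be assigned to the child for analysis".

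On the use of parent time, the Intervention section says that ELEVATE "will be administered one hour/day, four days/week, for twelve weeks", and Parent therapist partnership adds: "The parent and therapist will each deliver two days of intervention per week. The parent will attend the intervention sessions with the therapist".

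The cost-effectiveness section divides the difference in mean cost by the difference in GMFM-66 change, from the public payer and societal perspectives. It does not state the period over which costs are compared.

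**The concern.** Parent labour is a defining input of this intervention, since parents give half of the sessions and are present at the other half. Under the listed items, an hour of it reaches the societal cost only if it counts as lost productivity; out-of-pocket spending is the only other parent item. A session given in the evening, at a weekend, or by a parent who is on leave or not employed would ordinarily cause no lost productivity and so would carry no price. Children can enter from eight months of age, so some such families are plausible, although the article gives no proportion.

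The direction of any omission is clear. During the first six months only the Immediate group receives ELEVATE, so unpriced ELEVATE hours lower that group's societal cost and hence the incremental cost. If the effect on GMFM-66 is positive, the societal ratio looks more favourable than a full count of resources would make it. This is one perspective of a secondary analysis; the primary outcome comparison is not affected.

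**Working it through.** The article states no cost figure and no cost-effectiveness ratio, so there is no figure to reproduce. The check counts the hours and bounds their unpriced value.

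**Inputs**

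- Dose: 1 h a day, 4 days a week, 12 weeks (Intervention).
- Split: 2 days a week delivered by the parent and 2 by the therapist, with the parent attending the therapist's sessions (Parent therapist partnership).
- Parent wage *w*: not given; assumed 15 to 35 currency units per hour.
- Share *s* of parent hours counted as lost productivity: not given; taken from 0 to 1.

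**Hours per child**

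- All sessions: 1 × 4 × 12 = 48 h.
- Delivered by the parent: 1 × 2 × 12 = 24 h.
- Delivered by the therapist and attended by the parent: 1 × 2 × 12 = 24 h.
- Parent total: 24 + 24 = up to 48 h, against 24 therapist session hours.

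**Unpriced value per child:** *V* = *H* × (1 − *s*) × *w*, where *H* is 24 (delivery only) or 48 (delivery and attendance).

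| Share *s* counted as lost work | *H* = 24 h | *H* = 48 h |
|---|---|---|
| 0 | 24 × 15 to 24 × 35 = 360 to 840 | 48 × 15 to 48 × 35 = 720 to 1,680 |
| 0.5 | 180 to 420 | 360 to 840 |
| 1 | 0 | 0 |

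**Effect on the ratio.** With ratio = Δcost / Δeffect, leaving out *V* lowers the ratio by *V* / Δeffect. The article gives no expected difference in GMFM-66 points: the 0.91 under Sample size is a standardized effect with no standard deviation beside it. The shift in the ratio therefore cannot be put in figures from the document.

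**Effect of the horizon.** Suppose a share *q* of waitlist families completes ELEVATE within the costing period, with the same *s* and *w*. The unpriced difference between groups becomes *V* × (1 − *q*). At six months *q* = 0 by design. Over 12 months, for 48 h and *s* = 0, an assumed *q* of 0.5 gives 360 to 840, and *q* = 1 gives nil.

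**The case against.** The strongest reply is that this is a condensed article. Lost productivity is not defined in it, and the Resource Use Questionnaire, the cited human capital source and the earlier protocol that it follows are not shown. A broad definition could cover unpaid time. The word administration in the intervention cost might also be read as separate from therapist pay. This stands as a reason for caution, and if a broad definition applies, one clarifying sentence would largely meet the point. But the article does list the cost items, and on their ordinary meaning none prices an unpaid parent hour. The rule that assigns caregiver utilization to the child says where use is booked; it supplies no price.

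Other objections also stand in part:

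- Usual-care parents may spend time on therapy too, so the incremental hours may be fewer than 48.
- No six-month cost horizon is stated. Costs are collected over the study period, and waitlist families are offered ELEVATE after six months.
- The fidelity section mentions step counts during sessions but does not describe a log of parent hours.

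A reader might infer that the parent-delivered half is mostly costless in the analysis. The document does not support that, because the share of hours counted as lost work could be anything from none to all. A reader might also infer that the omission stops the trial from testing the Background remark on the cost-effectiveness of therapist-administered intensity. It does not: the comparator is usual care and there is no therapist-only arm, so no ratio from this trial could test that remark, with or without parent time.

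**Conclusion.** The point holds as a limitation of the stated costing rule for the societal perspective only. On the ordinary reading of lost productivity, the societal incremental cost of ELEVATE is understated by between nil and the full value of 24 to 48 parent hours per child. That full value is about 360 to 840 currency units for delivery alone, or 720 to 1,680 with attendance, at the assumed 15 to 35 per hour.

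The hours follow from the document. The wage and the share of hours outside paid work are assumptions, and the upper figures also take usual-care parents to spend no comparable time and waitlist families not to have trained within the costing period. No percentage of the intervention cost is given, because therapist pay is not stated and the counted cost also includes training, administration and materials.

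Omitting unpaid parent time from the payer perspective is normal practice and no fault. The remedy is a cheap improvement.

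**What to change.** In the societal perspective, report an analysis, at minimum a sensitivity analysis, that values parent time spent delivering and attending ELEVATE sessions:

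- Take hours from recorded sessions or, failing that, from the schedule (24 h delivered, 24 h attended), and show delivery alone and delivery plus attendance.
- Apply a stated wage, with a range.
- Subtract hours already counted as lost work, to avoid double counting. If those hours cannot be tied to ELEVATE sessions, show the results with none and with all of them subtracted.
- State what lost productivity covers, and over what period costs and effects are compared.

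Leave the payer perspective as it is.

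The cost is one cost line and one extra analysis, with no change to trial conduct. Scheduled hours serve if parent sessions are not logged. The downsides are a somewhat less favourable societal ratio and a wage assumption that must be defended.
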